### Design of the intervention – “the Informed Push Model”

The health system structure in Senegal follows a hierarchical model, with procurement centralised at the national level. Each of the 14 regional medical offices is responsible for overseeing the health districts within the region. Health districts typically include one health centre in the main town, as well as a network of predominantly rural health posts [37].

*The current supply chain model* (Fig. 2) is used to distribute most non-contraceptive medical commodities in Senegal, and is run by the central Senegalese supply programme (Pharmacie Nationale d’Approvisionnement, or PNA). Public Service Delivery Points (SDPs, i.e. health centres and health posts) submit stock requests to the district, which sends an aggregate order to the regional storeroom. Regional storerooms send aggregate orders to the national supply program, and after receiving supplies, prepare them for collection by the districts. Each SDP is then responsible for collecting their order from the district storerooms.

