## Methods

### Study setting

Senegal is a West African country with a population of approximately 14 million. It is classified as a lower-middle income country, with a Human Development Index rank of 163 out of 187 countries in 2013 [42]. Reproductive data are available from the 2014 Demographic and Health Survey [43], however we use data from the 2012–13 survey here to describe the context at the start of the intervention implementation. In Senegal, half (47 %) of women aged 25–29 were married at age 18 or below in 2012–13 [44]. The total fertility rate was 5.3 children per woman, with an average of 4.1 for women living in urban areas and 6.3 in rural areas [45]. Following the slow rise in modern contraceptive use reaching 12 % of WRAU in 2010–11, the MCPR increased to 16 % by 2012–13 (Fig. 1). An estimated 29 % of WRAU still had an unmet need for FP in 2012–13, implying that almost one third of women in union who did not want to get pregnant within the next 2 years were not using contraception [45].

Sharp differences existed in the MCPR between urban and rural areas (27 % compared to 9 %, respectively) and across educational levels (29 % among WRAU with secondary education and above, compared with 12 % among WRAU with no formal education). The most popular contraceptive method was injectables, accounting for 39 % of modern contraceptive users, followed by the pill (32 %) and implants (17 %) [45]. The public sector supplied the vast majority of contraceptives, with 83 % of modern contraceptive users obtaining their last method in a public SDP, and above 90 % for injectables and IUDs. The private sector supplied 13 % of users (predominantly condoms and pills) [44].

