### Outcome and impact evaluation (Objective 1)

Two sub-objectives will be addressed in the impact evaluation: (1.1) evaluate the effect of the intervention on contraceptive stock availability in SDPs, and (1.2) examine the effect of changes in stock availability on the MCPR at the population level. Table 1 presents the key outcome and impact indicators used for objective 1, based on data collected by two studies.

**Table 1 Tab1:** Indicators used for outcome and impact evaluation

Indicator	Data source
1. Stock availability in SDPs^a^	
Percentage of SDPs with all methods available on a given visit (%)	SDP survey; Service Provision Assessments [46]
Percentage of SDPs with each of the most popular short-, medium- and long-acting methods available on a given visit (%)	SDP survey; Service Provision Assessments
Percentage of the month/year stocked-out for any method (%)	SDP survey; Service Provision Assessments
Percentage of the month/year stocked-out for the most popular short-, medium- and long-acting methods (%)	SDP survey; Service Provision Assessments
Percentage of SDPs experiencing any contraceptive stock-out since intervention roll-out (%)	SDP survey
Average duration of stock-outs	SDP survey
2. FP^a^ consultations	
Monthly number of FP consultations	SDP survey
Monthly number of FP products distributed	SDP survey
Percentage of long-acting methods among monthly FP products distributed (%)	SDP survey
3. Contraceptive use	
Percentage of WRAU^a^ using a modern method^b^ of contraception (%)	Demographic and Health Surveys [48]
Percentage of single, sexually active WRA^a^ using a modern method of contraception (%)	Demographic and Health Surveys
Percentage of WRAU with an unmet need for FP (%)	Demographic and Health Surveys
Percentage of modern contraceptive users using a long-acting method^c^ (%)	Demographic and Health Surveys

^a^
*SDP* Service Delivery Point; *FP* family planning; *WRAU* Women of Reproductive Age in Union; *WRA* Women of Reproductive Age

^b^Modern methods include condoms, pills, injectables, implants, intra-uterine devices (IUDs), sterilisation

^c^Long-acting methods include implants and IUDs

The first study will follow a non-randomised stepped-wedge design using secondary data. To determine the impact of the intervention on contraceptive stock availability (objective 1.1) we will use data from Service Provision Assessments [46], nationally representative surveys of health facilities conducted annually in Senegal.

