A general mixed-effects logistic regression model will be constructed using an approach similar to the stepped-wedge analysis method outlined by Hussey and Hughes [47], although the rollout was not randomised. Stock availability will be modelled as a binary outcome variable (stock present or absent on the day of the survey) for all contraceptive methods, and as an ordinal variable for the number of each of the most popular short-acting (condoms and pills), medium-acting (injectables) and long-acting methods (implants and IUDs). Time will be treated as a fixed effect, and region as a random effect, to allow the intervention effect to vary regionally. Independent covariates at regional level, such as density of SDPs offering FP services and density of road network, will be used as well as SDP-level variables such as facility type.

Similarly, to examine the effect of the intervention on contraceptive use among WRAU (objective 1.2) we will use information on contraceptive use at the population level from the Demographic and Health Surveys [48], nationally representative surveys of women of reproductive age also conducted annually. As above, a mixed-effects logistic regression model will be built treating region as a random effect, and including woman-level covariates (such as education level) and regional covariates (such as pre-intervention MCPR). For both objectives, secondary analyses allowing for a delay in the effect of the intervention will be explored by allowing the variable for the intervention mode to be fractional.

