The second study will be a 4-year monthly time series of contraceptive stock availability (objective 1.1) and FP consumption (objective 1.2), constructed from data from a sample of SDPs. Five of the 13 regions where the intervention was implemented by 3PLs (i.e. excluding Saint Louis) will be randomly selected, and 10 districts randomly selected in each region with probability proportional to the number of SDPs in the district. In each selected district, the health centre will be included, as well as three randomly selected health posts, for a total sample of 200 SDPs across urban and rural locations. There is limited guidance on sample size calculations for time series analysis, which usually focuses on the number of time points rather than of sampling units [49]. At least 48 monthly observations on stock inventory and FP consultations will be collected from each SDP, as well as from the selected district and regional storerooms, and the national-level storeroom, ensuring at least 24 monthly time points pre- and post-intervention.

Information on contraceptive stock availability will be extracted from stock cards, daily patient registers and stock journals, as well as for several ‘tracer’ stocks (anti-malarials, oral rehydration salts, amoxicillin, and iron tablets) not expected to change as a result of the intervention. Monthly number of FP consultations in which patients receive a contraceptive at the SDP will be extracted from patient registers. A time series analysis will be conducted by constructing a generalised linear segmented regression model of the probability of stock-out for any method on a given month, and for the most popular short-, medium- and long-acting methods. We will examine whether there is a change in the slope or level of the number of methods available and monthly FP consumption at SDPs between the pre- and post-intervention periods. This analysis will be repeated for the tracer stocks to compare their change in stock availability with FP methods as a proxy measure of the ‘normal’ distribution channels through which these commodities are still distributed.

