Financial and economic costs will be categorised as: training and start-up costs, capital costs (including storage and transport equipment) and recurrent costs (such as staff salaries and maintenance expenditure). Capital costs will be estimated by using current (replacement) costs for all capital goods used in a year, annualised over the expected duration of their working life using a discount rate of 3 % according to World Health Organisation guidelines [60].

The aim of the cost-effectiveness study is to compare the incremental costs and incremental effects of the intervention compared to the current supply chain model for contraceptives. Since the intervention has already been rolled out, the pre-intervention costs of distributing FP commodities will be estimated by calculating costs of the current distribution system for non-contraceptive ‘tracer’ commodities (anti-malarials, oral rehydration salts, amoxicillin, and iron tablets). Estimates for the incremental effectiveness of the intervention compared to the current supply chain model will be obtained from the impact evaluation (objective 1). Several effect measures will be used to calculate incremental cost-effectiveness ratios (Table 3). Data on stock availability in SDPs will be used to calculate FP consumption lost due to stock­outs and the cost per stock­out averted for all stock­outs and for the most commonly used short­, medium­ and long­acting methods.

**Table 3 Tab3:** Indicators used for economic evaluation

Indicator	Data source
1. Cost measures	
Mean cost of delivery to SDPs^a^ and 3PLs^a^	SDP and district/regional/national storeroom survey and document review
Income from FP^a^ products sold	SDP and district/regional/national storeroom survey and document review
Income from FP consultation fees	SDP and district/regional/national storeroom survey and document review
2. Effectiveness measures	
Number of stock-outs averted for all products	SDP and district/regional/national storeroom survey and document review
Number of stock-outs averted for each of the most popular short-, medium- and long-acting product	SDP and district/regional/national storeroom survey and document review
Couple-years of protection provided	SDP survey and document review
Number of additional WRAU accessing modern contraception	SDP survey and document review, Demographic and Health Surveys [48]

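### Family planning consumption at public facilities is assigned to the population-use objective and is the only listed data source for couple-years of protection, so women moving from private to public supply may inflate that effect measure

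*Protocol article*

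**What the plan says.** All references are to the protocol article.

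- **Objective.** Under Outcome and impact evaluation (Objective 1), sub-objective 1.2 is to "examine the effect of changes in stock availability on the MCPR at the population level".
- **First study.** For this sub-objective, "we will use information on contraceptive use at the population level from the Demographic and Health Surveys". A woman counts as a user in these data whatever her source of supply.
- **Second study.** The time series covers "contraceptive stock availability (objective 1.1) and FP consumption (objective 1.2), constructed from data from a sample of SDPs". Its count is defined thus: "Monthly number of FP consultations in which patients receive a contraceptive at the SDP will be extracted from patient registers". The intervention section defines the facilities as "Public Service Delivery Points (SDPs, i.e. health centres and health posts").
- **Other source of supply.** Study setting reports that 83 % of modern users obtained their last method at a public SDP, and above 90 % for injectables and IUDs. It adds: "The private sector supplied 13 % of users (predominantly condoms and pills").
- **Economic evaluation.** Table 3 lists "Couple-years of protection provided" with the SDP survey and document review as its data sources and no DHS. "Number of additional WRAU accessing modern contraception" and the pregnancies, unsafe abortions and maternal deaths averted list DHS beside the SDP data. The text takes incremental effects from objective 1 without saying which of its two studies feeds which measure.
- **Limitations.** The Discussion names data quality, concurrent family planning activities and changes in the intervention. It does not mention a change in source of supply.

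**The concern.** A facility count and a population prevalence answer different questions. The intervention aims to end stock-outs at public SDPs. A woman who had been buying pills or condoms privately may then return to the public facility. The SDP count goes up, yet no woman has started contraception.

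The planned safeguards do not deal with this. Staggered rollout and the scoring of other family planning activities address confounding. Switching would be caused by the intervention itself, so it would follow the rollout dates region by region. The tracer commodities compare stock availability, not use.

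What is at stake is mainly the cost per couple-year of protection, because nothing in that measure's listed data sources would reveal switching. Any other effect measure that in practice is driven by SDP counts would be exposed in the same way.

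**Working it through.** **The plan's own figure.** 5 regions × 10 districts × (1 health centre + 3 health posts) = 200 SDPs, as stated. The figure is not in dispute. It confirms that the series consists of public facilities only.

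**Inputs (Study setting, 2012–13).** MCPR m = 16 % of women in union; public share P = 83 %; private share V = 13 %. The share s of private clients who switch is not given, so it is varied.

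**Starting position.** Public supply is 0.83 × 16 = 13.28 MCPR points. Private supply is 0.13 × 16 = 2.08 points.

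**Effect of switching with no new user.** The rise in public clients is s × V/P, and the apparent gain if this is read as use is m × V × s.

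| s | Rise in public clients | Apparent MCPR points | Change in true use |
|---|---|---|---|
| 10 % | 1.6 % | 0.21 | 0 |
| 25 % | 3.9 % | 0.52 | 0 |
| 50 % | 7.8 % | 1.04 | 0 |
| 100 % | 15.7 % | 2.08 | 0 |

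**Relative to a true effect.** If true use rises by d points, a count that includes switchers overstates new users by (d + m × V × s)/d. The values of d are illustrations, not estimates from the plan. At s = 25 %:
- d = 1: 1.52/1 = 1.52
- d = 2: 2.52/2 = 1.26
- d = 4: 4.52/4 = 1.13

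**By method.** For injectables and IUDs the non-public share is below 10 %, so the ceiling is below 0.10/0.90 = 11.1 %. Injectables (39 % of users) and implants (17 %) leave at most 100 − 39 − 17 = 44 % for pills and condoms. Suppose between half and all of the private 13 points lies there, and count the rest of the 44 as public. Full switching then raises public pill and condom clients by between 6.5/37.5 = 17 % and 13/31 = 42 %. The overall 15.7 % therefore hides concentration in these methods.

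**DHS estimate.** A woman who moves from a private to a public source is a user before and after, so the bias in MCPR is zero at every s.

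**The case against.** The strongest reply is that the plan already keeps the two quantities apart. Table 1 lists family planning consultations (SDP survey) and contraceptive use (DHS only) in separate blocks, and the main analysis of use is fitted to DHS. The second study's question is put as a change in consumption at SDPs, which is a facility-level description. This stands, and it limits the point.

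A reader might infer that contraceptive use and pregnancies averted *are* overstated. The article does not support that. Use is measured from DHS, and the pregnancies, abortions and deaths averted list DHS among their sources. Which input drives those models is not stated, and an article may leave this to the full plan. Nor does the article say that a woman turned away during a stock-out is counted as a non-user when lost consumption is calculated.

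The size is also open to challenge. The 15.7 % is a ceiling: it needs every private client to move. Setting 2.1 points against the rise in MCPR from 12 % to 16 % would mislead, because that rise is DHS-measured, so switching cannot inflate it, and it largely precedes the regional rollout. The effect on total couple-years also depends on conversion factors per method, which are not given; concentration in short-acting methods may reduce it. Finally, Table 1 gives key indicators only, so the lack of a split by source there does not prove that none is planned.

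The reply leaves three things in place: the objective 1.2 label on a public-facility count, the SDP-only data source for couple-years, and the omission of source switching from the limitations.

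**Conclusion.** The point holds in a limited form. Incremental couple-years of protection, as sourced in Table 3, may be overstated by movement from private to public supply, and so may any other effect measure driven by SDP counts. The direction is upward and the size is unknown. On the article's figures the artefact is a 3.9 to 7.8 % rise in public clients if a quarter to a half of private clients switch. Its ceiling is 15.7 %, or about 2.1 MCPR points, and it falls mainly on pills and condoms. The DHS-based MCPR effect is unaffected.

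These figures assume that the 2012–13 source shares apply to women in union, that they hold until the intervention arrives, and that switchers visit as often as existing public clients. A modest shift still matters because it is added to the incremental effect, which may itself be small.

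**What to change.** 1. In the second study, describe SDP consumption as public-sector distribution, not contraceptive use, and present it as supporting evidence for objective 1.2.
2. Fit the planned DHS mixed-effects model to public-source and to private-source modern use, by last source, as well as to total MCPR. The figures in Study setting show that last source is recorded.
3. Report couple-years of protection from SDP data as an upper bound, with a sensitivity range by method group for private-to-public switching, informed by the estimates in step 2. Do not simply subtract the whole fall in private-source use: other family planning activities run at the same time, and not all of that fall need be due to the intervention.
4. Drive additional users and pregnancies, abortions and deaths averted from the DHS change in use. Do not subtract switching again there, since that estimate is already free of it.
5. Add source switching to the limitations.

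The cost is extra analysis of survey data already in use, with no new fieldwork. Private-source estimates will be imprecise by region, so the sensitivity range is the minimum. The cost-effectiveness ratios may become less favourable.

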In many countries the supply chain is more complex than suggested by these models, with numerous actors at each level of the distribution system. Contraceptive supply chain systems in sub-Saharan Africa face a number of challenges, including poor infrastructure, inadequate forecasting, insufficient funds, delays in funding disbursement, long lead times, and political instability [6]. These challenges are compounded by the complex structural and institutional arrangements governing the distribution of medicines [12, 13], such as the presence of multiple donor-funded, programme-specific supply chains (such as for anti-malarial therapy or vaccines) running parallel to the national supply system. For example, in Senegal in 2009, the public sector supply chain had 11 main categories of health products at the central level, procured using 13 different sources of funding, through 12 different procurement organisations [14]. Despite these challenges, the performance of supply chain distribution is rarely monitored in-country. Periodic surveys indicate that FP stock availability is poor in public sector facilities in many countries. In 2013, UNFPA reported that an average of 55 % of facilities reported at least one contraceptive stock-out for any method in the previous 6 months in 12 countries in sub-Saharan Africa, ranging from 0.5 % in Ethiopia to 96.7 % in Cote d’Ivoire [6].

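### Anti-malarials are one of four tracers for the ordinary supply chain, but the Background gives them as an example of a parallel chain, and the protocol does not reconcile the two

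*Protocol article*

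**What the plan says.** The second study under Outcome and impact evaluation (Objective 1) extracts stock data for contraceptives and for four tracer products, "anti-malarials, oral rehydration salts, amoxicillin, and iron tablets) not expected to change as a result of the intervention". The segmented regression is repeated on the tracers, which serve "as a proxy measure of the ‘normal’ distribution channels through which these commodities are still distributed".

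Under Economic evaluation (Objective 4), "the pre-intervention costs of distributing FP commodities will be estimated by calculating costs of the current distribution system" for the same four products. The tracers are thus the stated basis of the pre-intervention cost in the incremental comparison.

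Two other places bear on whether all four products qualify:

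- The Background paragraph that opens its regional account with "Contraceptive supply chain systems in sub-Saharan Africa face a number of challenges" lists among the complications "multiple donor-funded, programme-specific supply chains (such as for anti-malarial therapy or vaccines) running parallel to the national supply system". The next sentence illustrates with Senegal in 2009: 11 product categories, 13 funding sources and 12 procurement organisations.
- The section on the design of the intervention says that the current supply chain model "is used to distribute most non-contraceptive medical commodities in Senegal". It does not list the exceptions.

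**The concern.** A tracer works as a control only if it shares the channel it represents. Here that is the chain in which facilities request stock through the district and collect it themselves. If a product is supplied through its own programme, its stock-outs follow that programme's funding and logistics, and its delivery cost is that of another chain.

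The article puts anti-malarials on the tracer list and also uses them as an example of a product with a parallel chain. If they did run on such a chain in Senegal, two results would be affected. The contraceptive-versus-tracer comparison in the time-series study could be pushed either way, depending on how malaria supply changed over the four years. The pre-intervention cost could also contain costs that contraceptives never incurred, and this would pass into the incremental cost-effectiveness ratios built on it.

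**Working it through.** The article gives no figure to reproduce. The check sets the statements side by side and then shows how far one product could move the control.

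**What each statement establishes**

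1. *Tracer list (Objective 1).* Four products, one of them anti-malarials. The article asserts that they still use the ordinary channel and gives no support for this.
2. *Cost proxy (Objective 4).* The same four products.
3. *Background.* Anti-malarial therapy is one of two examples of a parallel chain. The remark is about sub-Saharan Africa. The Senegal figures that follow count categories, funders and procurers; they do not mention anti-malarials or say how any product reaches a facility.
4. *Current model.* It carries most non-contraceptive commodities. Exceptions therefore exist, but nothing says that anti-malarials are among them.

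Statement 1 supports including anti-malarials and statement 3 raises doubt. Statement 4 leaves room for either. No sentence settles it.

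**How far one product could move the control**

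The article does not say whether the tracers are averaged, combined into an any-tracer indicator or modelled one by one. Let d be a change, in percentage points, confined to anti-malarials. The values of d below are assumptions.

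- *Equal-weight average:* shift = d/4. For d = 10, 10/4 = 2.5 points; for d = 20, 20/4 = 5 points.
- *Stock-out of any tracer*, assuming independent products with stock-out probability p in each of the other three: shift = d × (1 − p)³. With p = 0.10 the factor is 0.9³ = 0.729, giving 7.3 points (d = 10) to 14.6 points (d = 20). With p = 0.20 it is 0.8³ = 0.512, giving 5.1 to 10.2 points.
- *Each tracer modelled alone:* the other three series shift by 0, and a divergent anti-malarial series would be visible.

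If anti-malarial availability improved for reasons of its own, a contrast with the combined tracers would understate the intervention effect; if it worsened, the contrast would overstate it.

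**Cost**

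Suppose unit costs are averaged over four products with equal weight, and the anti-malarial cost is 50 % above that of the ordinary chain. The mean is then (1 + 1 + 1 + 1.5)/4 = 1.125, an error of 12.5 %. Both the weighting and the 50 % are assumptions. If only the ordinary chain's own resources are costed, the error could be smaller or absent.

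**The case against.** The strongest reply is that the article answers the question itself. Where it introduces the comparison it states that the tracers still travel through the ordinary channels. That statement is about this study and all four products, whereas the parallel-chain remark is regional background. Separate funding or procurement is also compatible with a shared last leg to the facility, and distribution to facilities is what the tracers represent. This stands, and it is why no error is shown. It does not close the matter: the route statement is a bare assertion, the Background speaks of parallel supply chains and not only of parallel funding, and the two are left unreconciled. Even with a shared last leg, separate upstream supply could cause stock-outs unrelated to the ordinary chain.

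A second reply is that little hangs on the tracers. For stock availability this is partly right. The stepped-wedge study relies on staggered regional rollout and uses no tracers, and the time series compares each contraceptive series before and after the intervention, with the tracers as an added comparison. For cost, the current system is micro-costed at several levels, but the tracers remain the named basis for the pre-intervention contraceptive cost.

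A third reply is that analysis by product is detail for an analysis plan. That is fair as to method. The product list, however, is fixed in this document.

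A reader might infer that anti-malarials in Senegal bypass the national chain, or that the intervention effect is biased by a calculable amount. The document supports neither. It gives no delivery route for anti-malarials in Senegal and no rule for combining tracers.

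**Conclusion.** The point holds as an unresolved tension in the choice of one control product. Anti-malarials may or may not meet the condition that a tracer must meet here, and the article contains statements pointing each way without reconciling them.

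The reach is limited to the control series of the time-series study and the pre-intervention cost comparator. The size cannot be determined from the document, because it depends on the actual route and on how tracers are combined. The d/4, any-tracer and 12.5 % figures illustrate sensitivity under stated assumptions and are not estimates of error. If each tracer is modelled separately, the doubt stays within one of the four series. The change is worth making because it is cheap and protects both comparisons.

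**What to change.** 1. Use the planned storeroom survey and the interviews with national, regional and district stock managers to establish how anti-malarials reached facilities over the four-year series, including any change of route. State the finding in the protocol or analysis plan.
2. Analyse each tracer as its own series.
3. Base the main tracer comparison and the comparator cost on tracers confirmed to use the request-and-collect chain. Apply the same test to oral rehydration salts, amoxicillin and iron tablets.
4. Report both the tracer comparison and the cost proxy with and without anti-malarials.

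The cost is mainly wording: stock data for all four tracers are already to be extracted, and each storeroom level is already to be visited. The downside is possibly one tracer fewer in the main comparison and slightly less precision.

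### Time-series study: fitting the tracer stocks separately gives no estimate or interval for the contraceptive-minus-tracer change

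*Protocol article*

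**What the plan says.** The plan is in the Protocol article, Methods, Outcome and impact evaluation (Objective 1), second study.

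- **Sample.** "Five of the 13 regions where the intervention was implemented by 3PLs (i.e. excluding Saint Louis) will be randomly selected", then "10 districts randomly selected in each region with probability proportional to the number of SDPs in the district"; within each district "the health centre will be included, as well as three randomly selected health posts, for a total sample of 200 SDPs". Each SDP contributes at least 48 months, with at least 24 before and 24 after the intervention.
- **Model.** The analysis is done by "constructing a generalised linear segmented regression model of the probability of stock-out for any method on a given month", and also for the most popular short-, medium- and long-acting methods. The quantities of interest follow: "We will examine whether there is a change in the slope or level of the number of methods available and monthly FP consumption at SDPs", before versus after the intervention.
- **Tracers.** Anti-malarials, oral rehydration salts, amoxicillin and iron tablets are not expected to respond to the intervention and are still supplied through the normal channels. For them, "This analysis will be repeated for the tracer stocks to compare their change in stock availability with FP methods as a proxy measure" of those channels.

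No joint model, interaction term or other estimator of the comparison is named. For the first study the same section names a mixed-effects model with region as a random effect. For the second it names neither a dependence structure nor a variance estimator.

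**The concern.** The tracers are the only comparison series named for this study. Their purpose is to show what would have happened to stock anyway, so the informative quantity is the contraceptive change minus the tracer change. As described, the analysis estimates each change and leaves the difference to be judged by eye or by comparing two significance results.

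This bears on attribution. If supply improved generally, both stock types would move, and chance alone could make one fit significant and the other not. The Discussion already concedes that attribution is hard for contraceptive use, because other family planning activities ran at the same time. Under Economic evaluation (Objective 4), the effect estimates from Objective 1 feed the cost-effectiveness ratios, including cost per stock-out averted.

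**Working it through.** **1. The plan's own figures.** 5 regions × 10 districts × (1 health centre + 3 health posts) = 200 SDPs, and 24 + 24 = 48 months. Both agree with the article. At SDP-month level this is 200 × 48 = 9,600 observations per outcome, though the article does not say whether the analysis is at that level or on an aggregated series. It gives no power calculation to reproduce.

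**2. What two separate fits provide.** Write b_F, s_F for the contraceptive change and its SE, and b_T, s_T for the tracers. The target is D = b_F − b_T, with

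SE(D) = √(s_F² + s_T² − 2·r·s_F·s_T),

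where r is the correlation between the two estimates. Both stocks are observed in the same SDPs and months, so r need not be zero. Neither separate fit estimates r, so a reader cannot recover the interval for D from the two sets of results.

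**3. Illustration (invented values).** b_F = −0.10, b_T = −0.06, both SEs 0.04.

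- Contraceptives: −0.10/0.04 = −2.5, significant at the 5% level.
- Tracers: −0.06/0.04 = −1.5, not significant.
- Difference: D = −0.04. With r = 0, SE(D) = 0.04 × √2 = 0.057, z = −0.71, 95% CI −0.04 ± 1.96 × 0.057, or about −0.15 to 0.07.
- With equal SEs, pairing multiplies SE(D) by √(1 − r): 0.84 at r = 0.3 (z = −0.85) and 0.63 at r = 0.6 (z = −1.12).

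The pair of results reads as an effect specific to contraceptives, yet the difference is not established at any of these correlations.

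**4. Why the joint model also needs a dependence structure.** The documents give no ICC or autocorrelation, so every correlation here is an assumption. Design: intercept, time, post and time since, over 48 months, on a linear-probability scale. With A = (X′X)⁻¹ and R the assumed correlation matrix, the ratio of true to independence SE is the square root of the diagonal of A X′RX A divided by that of A. Actual type I error at a nominal 5% is 2(1 − Φ(1.96/ratio)).

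| Assumed correlation | SE ratio, level | SE ratio, slope | Type I error, level / slope |
|---|---|---|---|
| AR(1) within SDP, 0.2 | 1.18 | 1.21 | 0.10 / 0.10 |
| AR(1) within SDP, 0.5 | 1.52 | 1.64 | 0.20 / 0.23 |
| AR(1) within SDP, 0.7 | 1.80 | 2.10 | 0.28 / 0.35 |
| Region-month shocks, ICC 0.01 | 1.18 | 1.18 | 0.10 / 0.10 |
| Region-month shocks, ICC 0.05 | 1.72 | 1.72 | 0.25 / 0.25 |
| Exchangeable within SDP, 0.05 | 0.97 | 0.97 | 0.044 / 0.044 |
| Exchangeable within SDP, 0.4 | 0.77 | 0.77 | 0.011 / 0.011 |

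The shock rows use 10 × 4 = 40 SDPs per region and no serial correlation; for example √(0.95 + 40 × 0.05) = √2.95 = 1.72. The exchangeable rows are √(1 − ICC). The direction therefore depends on the kind of correlation. Serial correlation and regional shocks make independence SEs too small; a stable SDP effect makes them too large for this within-SDP contrast.

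**The case against.** The strongest reply is that this is a condensed article whose full protocol and analysis plan are not shown. It says outright that the changes will be compared, and the formal estimator could well be specified elsewhere. It states no rule of the form: contraceptives significant, tracers not, therefore an effect. The evaluation also does not rest on tracers alone, because the Discussion relies on the staggered rollout and the parallel stepped-wedge study fits time as a fixed effect. Finally, tracers are called only a proxy. The Background mentions programme-specific chains, giving anti-malarial therapy as an example, and anti-malarials are among the tracers, so parallel trends cannot be taken for granted.

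Much of this stands. It rules out saying that the contrast is never to be estimated, and it means the contrast should not replace the uncontrolled change as the sole intervention effect. It does not remove the point: the method the article does state is a repeat of the same model, and a repeat cannot deliver the announced comparison with an interval.

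A reader might also infer that standard errors will ignore the repeated SDP data, that intervals will be too narrow, or that the sample will go unweighted. The document supports none of these. A generalised linear segmented model does not exclude random effects, GEE or robust variances, the unit of analysis is not stated, and weighting is simply not mentioned.

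**Conclusion.** The point holds for the tracer comparison. As described, separate segmented fits give no estimate or interval for the contraceptive-minus-tracer difference in level or slope change, although that difference is what the tracers are there to show. This follows from the stated method and needs no numerical assumption; the example only shows how far the pair of significance results can mislead.

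The dependence question is a requirement on the joint model and not a demonstrated error. If independence SEs were used, they would be too small by a factor of about 1.2 to 2.1 under the serial or regional correlations assumed in the table, and too large under purely exchangeable SDP correlation (ratio 0.77 to 0.97). The article does not say that independence SEs will be used.

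**What to change.** Fit contraceptive and tracer stock-outs in one segmented model with stock-type by level-change and stock-type by slope-change terms. Report those differences with 95% CIs alongside the uncontrolled contraceptive changes. State that the differences assume that contraceptives and tracers would otherwise have followed parallel trends.

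Inference should allow for the pairing of the two stocks within SDP, serial correlation over the 48 or more months, and shocks shared within region. One option is SDP random effects with autocorrelated errors plus region-by-month effects. The latter should be random, since fixed effects for every region and month would absorb an uncontrolled change that occurs region by region. Clustering by district alone would miss regional shocks, and five regions are too few to rely on region-clustered variances.

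The cost is analysis work only, since tracer data are already to be extracted. The contrast may have a wider interval than the contraceptive change alone: with equal SEs, SE(D) exceeds the single-series SE whenever r is below 0.5, because √(2(1 − r)) is then above 1.
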